### **4.5. PARTICIPANT IDENTIFICATION AND RECRUITMENT**

The identification of potential participants will involve the pre-screening of both electronic and paper notes to confirm their suitability to undergo cardiac surgery. Identification of participants who are suitable for the trial will take place by the PI and the direct care team at the pre-operative clinic in Hammersmith Hospital. The PI will remotely screen from the following recourses: pre-operative cardiac clinic lists, pre-appointment referral lists, cardiac surgical lists

at Imperial College Healthcare NHS Trust and weekly multidisciplinary team meetings. Additional members of the surgical will be added to the delegation log where appropriate, such as doctors working in the clinic. This will allow the supporting team members to refer patients from clinics to the research team.

The following data will be collected for the pre-screening:

- Full Name
- Age
- Hospital number
- Clinic appointment date and time
- Cardiac surgery provisional date and time

Patients and family members/friends will be identified and screened at the pre-operative clinic appointment before the surgery. These patients will be approached face-to-face, following ICHT guidelines and using appropriate personal protective equipment, if necessary. Participants will be given the patient information sheet in person and at least 24 hours to consider their participation in the research study (Annex II, III). Alternatively, potential participants may be contacted via telephone and introduced to the study after being initially approached by the clinical team. Those wishing to take part will be sent an information sheet and consent form via email or in the post (Annex IX). Participants will be asked to nominate a family member/friend and if they would be willing to give a participant information sheet to their chosen person (Annex IV, V). Their family members/friends will be given time to consider their participation and if happy will be consented by the study PI or other trained and delegated members of the study team. Patients will be also ask to select a personal consultee to be involved in situations where they might lack capacity to verbally consent to the study (e.g., delirium episodes). Consultees will be given time to consider their role in the study and will be asked to sign an information sheet (Annex XV, XVI).

Critical care nurses will be identified in ICU after providing direct care to at least one participant enrolled into the research study. They will be required to sign a written consent form (Annex VI, VII) and agree to comply with the study tasks as planned.

The study team will seek written informed consent before enrolling any participant into the study and consent will be dealt with as an ongoing process before any study task takes place. All participants will be then formally discussed with the CI and SIs to ensure their suitability for the study.

### Patients Regaining Consent

Patients undergoing cardiac surgery require mechanical ventilation and sedation to remain in an induced coma throughout the theatre procedure and for a short period of time after being admitted to ICU. Thus, patients' mental capacity is expected to fluctuate during the research study and patients will be unable to promptly re-consent to the study upon ICU admission.

The intra-operative stage is not included in the design for this research study; hence no direct study interventions will be performed on patients during this period. However, the research team may collect any relevant intra-operative information specified in the participant's electronic medical notes, which will happen retrospectively to the operation and written consent for data collection will be sought from participants prior to the procedure.

When appropriate, the study team will re-consent participants in ICU once they are clinically stable, fully awoken from the anaesthesia and have regained the capacity to remember and understand the details of the study. A member of the research team obtaining re-consent will offer to explain the study again and allow time for patients to reconsider their participation in the study. The study will then resume as planned in ICU when participants sign a Patient Regaining Capacity Consent Form (Annex VIII) and express that are happy to proceed with the study intervention in ICU. After written consent is obtained, a copy will be uploaded to medical records (e.g., Cerner), another copy will be given to the patient, and the original

document will be retained in the ISF, which will be stored in a key-locked cabinet inside the CI's office.

In occasions where participants are unable to consent or have lost their capacity to consent more than once whilst in ICU (e.g., delirium), their participation in the study will be considered by approaching their personal consultee. If their participation in the study resumes, videos / photos will be played at the patients' bedside during the planned intervention schedule. Upon delirium diagnosis, the last video played will be shown again to patients with the aim of promoting a reduction in ICU delirium. In the unfortunate eventuality of an urgent clinical deterioration (e.g., urgent induced coma due to mechanical ventilation requirements) that may happen whilst in ICU, their participation in the study will also resume considering their initial consent form signed before surgery and after seeking prior agreement with their personal consultee. In these situations, the Patient Regaining Capacity Consent Form will be collected at a later stage and after patients have re-gained capacity to express their wishes.

For patients who lose mental capacity after hospital discharge, they will be formally discussed with the CI and withdrawn from the research study. The study team will communicate the decision to participants and appropriately document it on medical notes.

### Personal Consultees

Personal consultees, who are interested in the patient's welfare but not doing so for remuneration or acting in a professional capacity, will be included in this research study. Consultees can be anyone within the patient's family or friend's group (e.g. relative/friend/partner). When possible, patients will delegate pre-operatively whom they would like to select as personal consultee.

Consultees will be introduced to the study post-operatively and in situations where patients lack capacity to verbalise their wishes (e.g., delirium). They will be given time to consider their role in the study and they will be provided with a study information sheet. If they agree to act as personal consultees for this study, the research team will ask them to consider whether patients would wish to continue taking part in the study or not. When an unanimous decision (between the research team and consultees) has been made, this will be clearly documented on patients' medical notes and consultees will be asked to sign a consent form.

If consultees agree that patients should continue in the study, their participation will resume. However, if personal consultees believe participants should be withdrawn from the study, the research team will respect their decision and make any necessary arrangements.

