## **6. STUDY ASSESSMENTS**

### **6.1. ASSESSMENT AND FOLLOW UP**

#### **STUDY INTERVENTION**

The intervention will require family members/friends (selected by patients) to self-record short videos (during the preoperative stage) based on a carefully drafted guided script divided into two parts: a) Reorientation (discussing date/time/surroundings, family members on the video); b) Reassurance (providing comforting/supportive messages). Videos will be recorded either with a video-recorder device (provided by the research team) in the pre-operative clinic or at home using a personal smartphone. At a later stage, videos will be sent to an encrypted NHS email and securely uploaded in line with ICHT Information Governance to a password-protected iPad, which will also facilitate family-patient video calls in ICU. In addition, patients will be requested to select personal pictures pre-operatively, which will be also sent to the PI's encrypted NHS email and securely uploaded into a special digital photo frame with reference to time and date.

Digital photos will be shown continuously at the patient's bedside for 12 hours a day (between 8am to 8pm) and different family videos will be played three times at specific hours of the day (9am, 2pm and 7pm) throughout their stay in ICU. Additionally, videos will be also played upon patient request and last video shown that day will be re-played. In occasions when patients develop ICU delirium and considering personal consultee's agreement, the last video shown to participants will be re-played and patients will be closely monitored. This will help the research team to understand if the combination of personal pictures and family videos impacted patients' orientation and reassurance and if, ultimately, promoted the reduction of ICU delirium. The PI will be responsible for setting up the required equipment and delivering the intervention alongside ICU nurses as illustrated in the study diagram below (Annex XI).

The draft guided script of reorientation and reassurance messages was initially developed based on published research and considering patients' memories from their lived ICU experience(s) [15]. Subsequently, it was further refined within a lay focus group of patient and public members (with ICU lived experience) and reviewed by an expert panel comprising two critical

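### The protocol conflicts on when the personal consultee is informed and on whether the delirium replay waits for the consultee's agreement, so a timely replay is not assured and the checklist cannot show why it was missed

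*Protocol*

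**What the plan says.** On when the consultee is informed, two sections differ.

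- Section 4.5, within recruitment before surgery, has the patient choose a consultee and continues: "Consultees will be given time to consider their role in the study and will be asked to sign an information sheet". It cites Annexes XV and XVI and gives no date.
- Section 4.6 (Personal Consultees) also has the patient name the consultee before surgery when possible, but then says: "Consultees will be introduced to the study post-operatively and in situations where patients lack capacity to verbalise their wishes (e.g., delirium"). It goes on: "They will be given time to consider their role in the study and they will be provided with a study information sheet". A unanimous decision with the research team and a signed form follow, and "If consultees agree that patients should continue in the study, their participation will resume".

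On the replay during delirium, three sections differ.

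- Section 3 has videos played when the patient shows signs of delirium and mentions no consultee.
- Section 4.6 (Patients Regaining Consent) says: "Upon delirium diagnosis, the last video played will be shown again to patients with the aim of promoting a reduction in ICU delirium".
- Section 6.1 (Study Intervention) says: "In occasions when patients develop ICU delirium and considering personal consultee's agreement, the last video shown to participants will be re-played".

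The trigger for approaching the consultee is also unclear. Section 4.6 (Patients Regaining Consent) words it as: "In occasions where participants are unable to consent or have lost their capacity to consent more than once whilst in ICU (e.g., delirium"). Sections 6.1 and 8.2 set no such threshold.

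**The concern.** The primary objective is the feasibility and acceptability of the intervention for both prevention and management of ICU delirium. The management part, the replay, is delivered only to patients who become delirious. Under Section 4.6 (Personal Consultees), these are the patients whose participation waits for someone who may be hearing of the study for the first time.

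Two things are at stake. The first is exposure: scheduled plays and the replay can be missed in the patients for whom management is being tested. The second is interpretation. The nurse checklist (Annex XII) asks whether the intervention was delivered three times (daytime item 3) and whether the video was replayed in delirium (daytime item 9a, night-time item 4a). Play times are written down, but nothing records that a play was withheld while awaiting the consultee. Such a miss is logged in the same way as one that staff could not deliver, although the two mean different things in a feasibility study.

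**Working it through.** The protocol gives no figure for this step, so there is none to reproduce. The check has two parts.

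**Following the text for one patient who becomes delirious.**

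1. Under Section 3 the video is played at signs of delirium, so nothing waits.
2. Under Section 6.1 the replay depends on the consultee's agreement.
3. Under Section 4.6 (Personal Consultees) that agreement needs an introduction to the study, an information sheet, time to consider, a joint decision and a signature. No time limit is set for any of these.
4. Under Section 4.5 the introduction and the time to consider could already have taken place.
5. The night-time checklist (items 4 and 4a) still expects an answer on replay between 8pm and 8am, when these steps are hardest to complete.

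Steps 1 and 2 cannot both be followed. Step 3 delays the replay by an unknown amount unless step 4 is what was meant.

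**Illustrating the size.** Inputs:

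- Patients: 12 (Section 7).
- Delirium incidence: up to 55% after cardiac surgery and 30–80% across ICU patients (Section 1.1). I use 30% and 55%; 30% is the lower end of the general ICU range.
- Scheduled plays: 9am, 2pm and 7pm (Section 6.1) on D1 to D3 (Annex I), so 3 × 3 = 9.
- Delay from delirium to the consultee's agreement: not given. Assumed range 0 to 48 hours.

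Expected number of delirious patients: 12 × 0.30 = 3.6 and 12 × 0.55 = 6.6. The chance of at least one at 30% is 1 − 0.70^12 = 0.986, so the rule would almost certainly come into use.

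Scheduled plays lost are those falling between onset and agreement:

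| Delirium found | Delay (assumed) | Plays lost | Of all 9 | Of those still due |
|---|---|---|---|---|
| D1, 8am | 0 h | 0 | 0% | 0 of 9 |
| D1, 8am | 2 to 6 h | 1 | 11% | 1 of 9 |
| D1, 8am | 12 to 24 h | 3 | 33% | 3 of 9 |
| D1, 8am | 48 h | 6 | 67% | 6 of 9 |
| D2, 8am | 24 h | 3 | 33% | 3 of 6 |
| D1, 8pm | up to 12 h | 0 | 0% | 0 of 6 |
| D1, 8pm | 24 h | 3 | 33% | 3 of 6 |

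In every row with a delay above zero, the replay itself is late if it waits for agreement, even where no scheduled play is lost.

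**The case against.** The strongest reply is that this is a wording inconsistency around a deliberate safeguard, and that its consequences are easily exaggerated. Much of that stands.

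- **A pause is not unique to delirium.** Section 4.6 (Patients Regaining Consent) holds every patient after surgery until the re-consent form is signed, and sends patients with urgent deterioration to the consultee too. Delirium adds a step to one that everyone faces.
- **Delirium data need not be lost.** A reader might infer selective loss of outcome data. CAM-ICU is recorded twice daily as usual care (Section 3), ICU clinical data are routine (Section 6.1), and consent before surgery covers medical-record information. A consultee may withdraw a patient (Section 4.4), but nothing withdraws anyone when delirium starts. Automatic withdrawal for lost capacity applies only after hospital discharge.
- **Replay is not shown to be impossible.** No delay is stated. The consultee may be any relative or friend, possibly the person who recorded the videos, and could agree quickly. The sentence on replay at diagnosis follows a condition that participation has resumed, so it may describe patients already cleared.
- **A first episode may be exempt.** The threshold of more than one loss of capacity can be read that way. However, the same sentence also covers any patient unable to consent, so it does not settle the matter.
- **Reporting by waiting period could sit in a statistical analysis plan.** That is fair. The checklist is a protocol annex, though, and a reason not recorded there is not readily recovered at analysis.

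None of this removes the conflict between the sections, or the fact that any exposure lost to this added step falls on patients who become delirious.

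**Conclusion.** The point holds as a conflict that the sponsor should resolve. Sections 3, 4.5, 4.6 and 6.1 do not agree on when the consultee is informed or whether the replay waits for agreement. Under the wording of Section 4.6 (Personal Consultees), timely replay is not assured. At risk are intervention exposure, the replay, and the meaning of daytime items 3 and 9a and night-time item 4a. Delirium status is not.

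The size is unknown. On the assumed delays it runs from none of the 9 scheduled plays to 6 of them in an affected patient, depending on the delay and the hour of onset.

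A reader might multiply a one-day delay through to a loss of 3/9 × 0.30 = 10% to 3/9 × 0.55 = 18% of all scheduled plays. The documents do not support that as an estimate: the 24 hours is assumed, and three plays are not lost in every case. Nor would such a loss by itself turn the delivery record into one mainly about patients without delirium. If each delirious patient kept 6 of 9 plays, their share of delivered plays would fall from 30% to 1.8/8.1 = 22%, or from 55% to 3.3/7.35 = 45%.

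**What to change.** 1. **Reconcile Section 3, Section 4.5, both parts of Section 4.6, and Section 6.1.** State once whether a first episode of delirium triggers the consultee step, and whether the replay waits for the consultee's agreement. Which rule applies is for the sponsor to decide; the sections need to state the same one.
2. **Amend Section 4.6 (Personal Consultees) in line with Section 4.5.** Suggested sense: where possible, the consultee chosen by the patient receives Annex XV and confirms willingness to act before surgery, so that only advice on continuing has to be sought if capacity is lost. The consultee's role and power to withdraw the patient stay as they are.
3. **Add a reason to the checklist in Annex XII** at daytime items 3 and 9a and night-time item 4a: not played because consultee advice was awaited. These misses can then be kept apart from failed delivery.

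The cost is a short amendment, earlier use of an existing information sheet, and one added response on a form. The downside is briefing up to 12 consultees, some for patients who never lose capacity.

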### **4.4. WITHDRAWAL CRITERIA**

#### PARTICIPANTS WITHDRAWAL CRITERIA

- No longer willing to participate after consent
- Personal consultee wishing to withdraw participants from the study
- Patients that the clinical and/or research team deem too distressed to continue participating in the study
- Participants who have lost capacity to participate in the study after hospital discharge

For participants wishing to not continue in the research study their decision will be respected. Participants will be reassured that their wishes will not affect their care and/or employment in any way. They will also be informed that they are not required to give a reason with regard to not wishing to participate. However, if they are happy, the reason will be recorded in their medical records.

When conducting clinical research, the study team will always respect participants' interests and prioritise them over those of science and society. Therefore, if the participant wishes to be withdrawn from the study, this must be done without delay and appropriately documented in the medical notes. The research team will respect participants' wishes and feelings by ensuring that no study activities are done to and/or carried out in relation to participants who object to continuing in the study. Those participants wishing to withdraw will be asked for permission to keep the data already collected, but if they decline, all data will be destroyed appropriately.

The study team will also assume the professional responsibility to protect participants from the risk of harm and/or prevent them from feeling pain or discomfort. Additionally, the Principal Investigator in agreement with the Chief Investigator will also consider withdrawing any participant who appears to be in too much distress throughout the research study. If so, this will be discussed with the participant and clearly documented on medical notes.

Participants who lose capacity after hospital discharge or die unexpectedly during the course of the study will be automatically withdrawn. If they are withdrawn, any identifiable data already collected with consent will be retained and may be analysed, but no further data will be collected, or any other research procedures carried out in relation to these patients.

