### Participants Unable to Consent

A participant is deemed unable to decide whether to take part in research if they cannot:

- Understand the information relevant to the decision (information should be given in a way that is appropriate to the particular participant)
- Retain that information for long enough to conclude the decision (this may be for a relatively short time, but still long enough to enable decision-making to occur)
- Use or weigh that information as part of the process of making the decision (participants need to understand the consequences of each option).
- Communicate their decision (whether by talking, using sign language or any other means).

Due to the specificity of the care group, patient's mental capacity is expected to fluctuate throughout the study and if so, a personal consultee will be included to decide whether patients should continue taking part in the research study. A Patient Regaining Capacity Consent Form should be signed post-operatively when possible, ideally before participants resume with the study in ICU, and after periods of lacking capacity.

Decisions whether or not the participants have the capacity to give consent will be made by the PI or a Senior Researcher, who has appropriate training and experience in assessing consent. The PI has been formally trained on how to obtain informed consent from participants and aware of the Mental Capacity Act 2005.

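### A consultee's refusal while the patient lacks capacity in ICU counts as withdrawal, and no text says the patient is asked again once capacity returns, so any such loss falls mainly on patients with delirium

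*Protocol*

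**What the plan says.** **The consultee's decision.** Protocol 4.4 lists this among the withdrawal criteria: "Personal consultee wishing to withdraw participants from the study". Section 4.6 (Personal Consultees) adds that "if personal consultees believe participants should be withdrawn from the study, the research team will respect their decision and make any necessary arrangements". Section 8.2 (Participants Unable to Consent) says that "a personal consultee will be included to decide whether patients should continue taking part in the research study". None of the three distinguishes a passing loss of capacity from a lasting one.

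**When the consultee is approached.** Section 4.6 (Patients Regaining Consent) gives the main trigger: "In occasions where participants are unable to consent or have lost their capacity to consent more than once whilst in ICU (e.g., delirium" being its example. Urgent clinical deterioration is a second trigger, for which "their participation in the study will also resume considering their initial consent form signed before surgery and after seeking prior agreement with their personal consultee". Section 6.1 also makes replaying the video in delirium subject to the consultee's agreement.

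**The patient's own consent.** Section 4.5 states: "The study team will seek written informed consent before enrolling any participant into the study". Section 8.2 expects capacity to vary: "patient's mental capacity is expected to fluctuate throughout the study and if so, a personal consultee will be included".

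**The regained-capacity form (Annex VIII).** Section 4.6 uses it to resume after anaesthesia, and later for patients who continued through a deterioration with consultee agreement. Section 8.2 is more general: "A Patient Regaining Capacity Consent Form should be signed post-operatively when possible, ideally before participants resume with the study in ICU, and after periods of" incapacity.

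**Data after withdrawal.** Section 4.4 has one rule for participants who themselves wish to leave (data kept with permission, otherwise destroyed). It has another for capacity lost after hospital discharge and for death (data retained, nothing further collected).

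**The concern.** A patient may agree in writing, become delirious for a short time, be withdrawn by a consultee, and recover while still in hospital. Followed as written, the protocol then has no stated step that asks this patient anything.

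The patient's own interviews begin on the day of ICU discharge. Ward CAM, MoCA, GAD-7 and PHQ-9 come after ICU (6.1 and Annex I). Withdrawal in ICU, in its ordinary meaning, therefore comes before all of them.

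Acceptability is part of the primary objective (2.1), and the views of patients who became delirious are central to it. If some of them leave because they became delirious, the follow-up results and interview themes tilt towards patients who did not.

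The data rule is also incomplete. Consultee withdrawal in ICU fits neither rule in 4.4, because a patient without capacity cannot be asked for permission and the retention rule is written for other situations.

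**Working it through.** **Step 1: is there a stated way back?** The four uses of consent after incapacity, side by side:

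| Situation | Stated step |
|---|---|
| Waking from anaesthesia (4.6) | Annex VIII form, then the study resumes |
| Consultee agrees to continue (4.6) | Participation resumes |
| Urgent deterioration, consultee agrees (4.6) | Participation resumes; Annex VIII form collected later |
| Consultee refuses (4.4, 4.6) | Withdrawal; no later step given |

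The general wording in 8.2 could be stretched to the last row, but it speaks of participants and of resuming, and does not mention a patient whom a consultee has withdrawn. Two researchers could act differently on the same text.

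**Step 2: inputs for the size.**
- n = 12 patients (sections 3 and 7). The plan's total reproduces: 12 + 12 + 6 = 30. The protocol gives no expected loss, so there is no figure of its own to check against.
- p = delirium rate. Section 1.1 gives up to 55% after cardiac surgery, and 30–80% as a general range.
- r = consultee refusal rate. It is not in the protocol; 10%, 25% and 50% are assumptions.
- Simplifications: every patient with delirium goes to a consultee, nobody else does, and there is no other dropout. If only some patients with delirium reach a consultee, read r as the proportion reached times the proportion refused.

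**Step 3: formulas.**
- Expected losses = n·p·r
- Probability of at least one loss = 1 − (1 − p·r)^12
- Delirious share of those still followed = p(1 − r)/(1 − p·r)

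**Step 4: results at p = 55%** (12 × 0.55 = 6.6 patients expected with delirium).

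| r (assumed) | Expected losses | P(at least one) | Delirious share of those followed |
|---|---|---|---|
| 10% | 6.6 × 0.10 = 0.66 | 49% | 0.495/0.945 = 52.4% |
| 25% | 6.6 × 0.25 = 1.65 | 83% | 0.4125/0.8625 = 47.8% |
| 50% | 6.6 × 0.50 = 3.3 | 98% | 0.275/0.725 = 37.9% |

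**Step 5: range over p, at r = 10%, 25%, 50%.**
- p = 30%: 0.36, 0.9, 1.8 losses; share followed 27.8%, 24.3%, 17.6%.
- p = 80%: 0.96, 2.4, 4.8 losses; share followed 78.3%, 75.0%, 66.7%.

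Under these assumptions the share is always below p. How far below depends on r.

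**Step 6: effect of asking again.** If every such patient regained capacity and agreed to rejoin (assumption), losses by this route would be zero. If half rejoined, they would halve: at p = 55% and r = 25%, from 1.65 to about 0.8.

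**The case against.** The strongest reply is that respecting a consultee is a protective choice, not an error, and that a refusal is itself information about acceptability in a 12-patient single-group feasibility study. The consultee is chosen by the patient where possible and is asked what the patient would wish. That stands: the consultee's power to stop the study is not criticised here. The gap is what happens afterwards.

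Several stronger readings are tempting, and the document does not support them:

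- *The protocol bars return.* It is silent. Section 8.2 asks for the form after periods of incapacity, and consent is described as ongoing. The diagrams in Annexes XI and XIV and the Annex VIII form itself were not available to check and may show such a step.
- *Delirious patients as a group are lost.* Only those whose consultee refuses are lost.
- *Only delirious patients are exposed.* Urgent deterioration and other inability to consent also lead to the consultee.
- *All interviews are lost.* Relatives and friends consent separately and may be interviewed alone.
- *Delirium incidence is necessarily biased.* CAM-ICU results recorded before the refusal may still count. Nothing says they are destroyed.
- *The unanimity between team and consultee in 4.6 contradicts the consultee's right to withdraw.* It can be read coherently: both must agree to continue, and a refusal alone stops participation. It needs clarifying, but it is not a proven conflict.

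**Conclusion.** The point holds in a limited form. A consultee's refusal in ICU is an unqualified withdrawal of a patient who has already consented in writing, and the text does not link that decision to the regained-capacity process. Because delirium is the main named trigger, losses by this route fall disproportionately on patients with delirium and remove their own post-ICU assessments and interviews.

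The direction is clear, but the size is not known. At 55% delirium the expected loss runs from about 0.7 to 3.3 of 12 patients over assumed refusal rates of 10% to 50%. At the low end the effect on the followed group is small (55% to 52%); at the high end it is large (55% to 38%). These figures rest on the assumed refusal rates and the simplifications in the working, and are not forecasts. The point deserves action because the remedy uses a form that already exists.

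**What to change.** In Protocol 4.4 and 4.6, with 8.2 brought into line:

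1. State that a consultee's refusal stops all study activity for as long as the patient lacks capacity.
2. If capacity returns before hospital discharge, ask the patient on the Annex VIII form whether to rejoin the follow-up assessments and interviews, and whether data already collected may be kept.
3. If capacity has not returned by then, let the consultee's decision stand as withdrawal, and state what happens to the data.
4. Leave the other withdrawal criteria in 4.4 unchanged.
5. Clarify that continuing needs the agreement of both team and consultee, while the consultee's refusal alone is enough to stop.
6. Report consultee withdrawals by delirium status.

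The consultee's control while the patient lacks capacity is untouched. The cost is one extra approach to a recovering patient and an ethics committee amendment. Because a withdrawal criterion changes, it should be assessed under section 9 (Protocol Amendments), which requires committee approval before a substantial amendment takes effect.
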